The T0 (baseline) assessment phase has a duration of approximately 37 minutes, is the same for all participants, and is administered at the Virtual Reality Laboratory (A10-A11), Department of General Psychology, University of Padova (Italy). In this phase, the following measures are administered: (1) a demographic schedule (addressing age, gender, nationality, mother tongue, marital status, years of school attendance, employment status, psychological problems or disorders, ongoing psychological treatment, drug use, medical conditions, neuromuscular issues, previous injures, previous experiences in relaxation practice or anxiety management training, or with Oculus), and also, refraining from smoking, intense physical exercise, consuming caffeine for at least 1 hour before testing, and consuming alcohol for at least 6 hours before testing [42]; (2) a series of self-report questionnaires investigating depression, anxiety, stress, quality of life, and distress coping strategies (State Trait Anxiety Inventory-Y [STAI-Y], Depression Anxiety Stress Scales-21 [DASS-21], Psychological General Well-Being Index [PGWBI], and COPE-NVI); and (3) resting heart rate detection with an Mi Band 2 sensor.

Before and after each relaxation session (t1-t4), in approximately 20 minutes, the personal level of tension is assessed by using a visual analog scale from 0 (no tension) to 10 (extreme tension level). The state-anxiety level is evaluated based on the STAI-Y1. The 4 relaxation sessions are administered 2 to 3 days apart from each other for all 3 groups. The assessment phase is administered through Moodle, an e-learning platform used for data collection.

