The T1 phase (day 7) required approximately 60 minutes. Before and after the relaxation session, states of tension and anxiety are assessed by using a 0 (no tension) to 10 (extreme tension level) scale, and the state-anxiety level is evaluated based on the STAI-Y1. Then, participants are exposed to a PMRT session merged with a VR or a GI procedure. Before the GI or the VR experience, all the participants fill out the Vividness of Visual Imagery Questionnaire and the Test of Visual Imagery Control. After the PMRT session, users compile a series of self-report questionnaires investigating depression, anxiety, stress, and quality of life (STAI-Y, DASS-21, PGWBI), and the VR group only fill out the Virtual Reality Sickness Questionnaire to monitor VR-related side effects (eg, sickness) and the ITC-SOPI to assess the sense of presence at the end of the T1 phase. The Mi Band 2 sensor is used during the entire T1 phase administration to detect resting heart rate activity. This assessment phase is administered through the Moodle e-learning platform.

The T2 phase (follow-up) is deployed for approximately 45 minutes. Before and after the relaxation session, states of tension and anxiety are assessed using a visual analog scale from 0 (no tension) to 10 (extreme tension level). The state-anxiety level is evaluated based on the STAI-Y1. All the users are exposed to a self-GI experience in which those who were part of the VR group are asked to recall the personalized VR scenario experienced during the T1 phase (day 7). Instead, the GI group retrieve the image participants had used in association with the PMRT during the T1 phase (day 7). After the session, participants fill out a series of self-report questionnaires investigating depression, anxiety, stress, quality of life (STAI-Y, DASS-21, PGWBI), and an ad hoc version based on the ITC-SOPI to assess the sense of presence experienced during the imagery experience. This assessment phase is administered based on the Moodle e-learning platform. The Mi Band 2 sensor is used during the entire T1 phase administration (day 7) to detect resting heart rate activity.

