### Power Calculation

Sample size estimation was computed with G*Power 3.1 software (Heinrich Heine Universität Düsseldorf) [43]. As a statistical test, the repeated-measures ANOVAs between factors have been considered. The effect size was set as 0.25, the α as .05, and the Power (1β error probability) as 0.80. We have 3 separate groups and 3 measurements. On the basis of these parameters, we estimated having to recruit at least 36 participants for each of the 3 groups.

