### Measures-Screening and Primary Outcomes

In Table 1, all the assessment and primary outcome measures are described.

**Table 1 table1:** Evaluation tools and methods by outcome of interest.

Primary objective	Description	Evaluation tool
1. Number of participants with virtual reality (VR)–related side effects as assessed by the Virtual Reality Sickness Questionnaire (VRSQ) and the investigators’ observations^a^	Participants in the 2 VR experimental arms (Interventions A and B) are asked to refer to whether the VR head-mounted display was painful, too heavy, or uncomfortable. Participants are asked if they have experienced negative side effects during the VR exposure based on the VRSQ, administered at the end of the VR exposure. This questionnaire is based on a dichotomous answer (Yes/No). During the VR experience, the investigator observes participant reactions and records the behaviors and signs that suggest an unpleasant experience.	VRSQ [44,45]
2. Changes between and within subjects in depression scores^b^	Differences between groups and change from baseline to the T1 and T2 phases in depression scores are assessed based on the Depressive Anxiety Stress Scale-21 (DASS-21-Depression Subscale). Items are answered using a 4-point Likert scale (0-3). Scores range from 0 to 42 (the scores will need to be multiplied by 2 to calculate the final score). Higher scores indicate more severe depression.	DASS-21-Depression Subscale [46-48]
3. Change is being assessed between and within subjects in trait-anxiety scores^b^	Differences between groups and change from baseline to the T1 and T2 phases in trait-anxiety scores are assessed based on the State-Trait Anxiety Inventory-Y2 (STAI-Y2, Trait Anxiety). The measure is a self-report questionnaire investigating trait anxiety based on a 4-point Likert scale (1-4). Scores range from 20 to 80. Higher scores indicate higher trait-anxiety severity.	STAI-Y2 [49-51]
4. Changes between and within subjects in state-anxiety scores^b^	Differences between groups and change from baseline to the T1 and T2 phases in state-anxiety scores are assessed based on the State-Trait Anxiety Inventory-Y1 (STAI-Y1, State Anxiety) before and after each session. The STAI-Y1 is a self-report questionnaire investigating the state anxiety based on a 4-point Likert scale (1-4). Scores range from 20 to 80. Higher scores indicate greater state-anxiety severity.	STAI-Y1 [49-51]

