9. Change is being assessed between and within subjects in quality-of-life scores^c^	Change from baseline to the T1 and T2 phases in quality-of-life scores on the Psychological General Well-Being Index (PGWBI) is assessed at 3 different assessment times. The measure consists of 22 self-administered items, rated on a 6-point scale (0-5), which assesses psychological and general well-being. Scores range from 0 to 110. Higher scores indicate greater well-being.	PGWBI [53-55]
10. Change is being assessed between and within subjects in coping strategies scores^b^	Change from baseline to the T1 and T2 phases in coping strategies is assessed at 3 different assessment times. The Coping Orientation to the Problems Experienced-New Italian Version (COPE-NVI) is a self-report questionnaire developed to assess the different coping strategies people use in response to stress; it is based on 60 items rated on a 4-point scale (1-4). Total scores range from 60 to 240. Higher scores indicate that a certain coping strategy is frequently used by the person.	COPE-NVI [56]
11. Change is being assessed between and within subjects in sense of presence scores related to the VR and guided imagery experiences^c^	Differences between groups and change from the T1 and T2 phases in sense of presence related to the VR or guided imagery experience are assessed at 2 different assessment times based on a visual analog scale and the ITC-Sense of Presence Inventory (ITC-SOPI). The ITC-SOPI is a self-report questionnaire assessing the sense of presence. Items are rated on a 5-point Likert scale (1-5). Scores range from 36 to 180. To obtain the scores for each of the scales, the average of the items is calculated. Higher scores indicate a higher sense of presence.	ITC-SOPI [57]; Visual analog scale-sense of presence
12. Change is being assessed between and within subjects in heart rate^b^	Differences between groups and change from baseline to the T1 and T2 phases in heart rate are assessed based on the Xiaomi Mi Band 2 sensor. It is used in 3 different assessment times (T0, T1, T2). During T1 and T2 heart rate is measured before, during, and after the in-presence relaxation session.	Xiaomi Mi Band 2 tool [58,59]

^a^T1 (day 7) phase.

^b^T0 (baseline), T1 (day 7), and T2 (day 14) phases.

^c^T1 (day 7) and T2 (day 14) phases.

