### Statistical Procedure and Data Analysis

Quantitative statistical analyses will be performed using SPSS (versions 27.0 and 28.0; IBM Corp) [60,61] and R package [62]. To investigate the normal data distributions of the dependent variables, ranges of skewness and kurtosis will be determined. The Kolmogorov-Smirnov and the Shapiro-Wilk tests will also be performed to evaluate the statistical significance (mean, 95% CI) and normality of the distributions. In addition, Cronbach α will be assessed for each self-report questionnaire’s subscales. To explore sociodemographic features, frequencies, means, and SDs will be measured.

To examine differences between and within subjects, the 3 groups will be evaluated by a repeated-measures ANOVA for mixed designs, where individuals will be the random effect, while the type of intervention and time (T0/T1/T2/before and after each session) will be the fixed effects. The Akaike information criterion and binary logistic regression will be performed to explore significant influence factors.

Spearman rank correlation coefficient will be used to investigate the relationship between the self-reported measures and heart rate.

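### One person-level random effect over a time term that mixes visits with before/after readings gives the T1 pre-to-post VR v GI contrast the wrong error: probably too wide, by an amount that rests on undocumented correlations

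*Protocol article*

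**What the plan says.** The analysis section of the protocol article states that "the 3 groups will be evaluated by a repeated-measures ANOVA for mixed designs", and that "individuals will be the random effect, while the type of intervention and time (T0/T1/T2/before and after each session) will be the fixed effects". It names no session-within-person effect, covariance structure or sphericity correction.

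State anxiety is read often. Table 1, outcome 4, has it "assessed based on the State-Trait Anxiety Inventory-Y1 (STAI-Y1, State Anxiety) before and after each session". Study Design says the same of the four training sessions ("Before and after each relaxation session (t1-t4), in approximately 20 minutes, the personal level of tension is assessed", with STAI-Y1 named in the next sentence) and of T1 and T2. With one reading at T0 this makes 1 + 2 × 6 = 13 STAI-Y1 readings per person, or 1 + 2 × 2 = 5 if only T0, T1 and T2 are modelled. The relaxation visual analog scale is also taken before and after each session.

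On spacing, "The T1 phase (day 7) required approximately 60 minutes", so the two T1 readings are about an hour apart at most. The Table 1 footnote puts the phases at "T0 (baseline), T1 (day 7), and T2 (day 14) phases".

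**The concern.** A random effect for the person with independent residuals implies equal variances and one common correlation for all pairs of readings. Every within-person contrast is then judged against one pooled error. That error is right for all contrasts only if readings an hour apart correlate exactly as strongly as readings a week or two apart, which would be a coincidence.

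The contrast most exposed is the fall in state anxiety across the T1 session, VR v GI. It is the closest to the main hypothesis, and the preliminary analysis in Results already looks at it. If its error is too large, a real VR benefit is easier to miss. If the error for change from T0 is too small, that contrast gives extra false positives.

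**Working it through.** **The plan's own figure.** Power Calculation says "The effect size was set as 0.25, the α as .05, and the Power (1β error probability) as 0.80", with 3 groups and 3 measurements, for the between-factors test. With an assumed correlation of 0.5 (none is given), λ = f²·N·m/(1 + (m − 1)ρ) = 0.0625 × 108 × 3 / 2 = 10.125 on (2, 105) degrees of freedom. Power is 0.809, and 108 is the smallest balanced total reaching 0.80. The stated 36 per group reproduces and is not in dispute.

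**Inputs.** From the article: 36 per arm, 13 or 5 readings. Assumed: equal variances (SD 1), same-session correlation ρw, cross-session correlation ρb, true pre-to-post difference 0.5 SD between two arms. Power uses the normal approximation.

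**Formulas.** For the difference between readings i and j, compared between two arms of 36:
- true SE = √[2 × 2(1 − ρij)/36]
- SE under the person-only model = √[2 × 2(1 − r̄)/36], where r̄ is the mean of all pairwise correlations
- ratio = √[(1 − r̄)/(1 − ρij)]

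**Worked case, 13 readings, ρw 0.7, ρb 0.5.** Of 78 pairs, 6 are same-session and 72 cross-session.
- r̄ = (6 × 0.7 + 72 × 0.5)/78 = 0.515.
- Model SE = √(4 × 0.485/36) = 0.232; true SE = √(4 × 0.3/36) = 0.183; ratio 1.27.
- Power with the contrast's own error: Φ(0.5/0.183 − 1.96) = 0.78.
- Power with the pooled error: Φ((0.5 − 1.96 × 0.232)/0.183) = 0.60.
- Rejection rate under no effect: 2[1 − Φ(1.96 × 1.27)] = 1.3%.

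**Range** (SE ratio = model/true; above 1 is too wide):

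| Readings | ρw / ρb | Pre-to-post T1 ratio | Power, pooled v own error | T0 to T1-post ratio | Type I error, T0 to T1-post |
|---|---|---|---|---|---|
| 13 | 0.6 / 0.5 | 1.11 | 0.58 v 0.66 | 0.99 | 5.2% |
| 13 | 0.7 / 0.5 | 1.27 | 0.60 v 0.78 | 0.98 | 5.4% |
| 13 | 0.8 / 0.5 | 1.54 | 0.63 v 0.92 | 0.98 | 5.6% |
| 13 | 0.8 / 0.3 | 1.82 | 0.42 v 0.92 | 0.97 | 5.7% |
| 5 | 0.6 / 0.5 | 1.10 | 0.59 v 0.66 | 0.98 | 5.5% |
| 5 | 0.7 / 0.5 | 1.24 | 0.62 v 0.78 | 0.96 | 6.0% |
| 5 | 0.8 / 0.5 | 1.48 | 0.67 v 0.92 | 0.94 | 6.6% |
| 5 | 0.8 / 0.3 | 1.73 | 0.48 v 0.92 | 0.93 | 7.0% |

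**Reverse case, 0.4 / 0.5.** Pre-to-post ratio 0.92-0.93 (type I error about 7%); T0 to T1-post ratio 1.01-1.02.

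**Correlation decaying over time.** Take 13 readings, same-session 0.7, and 0.5 between adjacent sessions falling by 10% per session step. The T0-T2 correlation is 0.5 × 0.9⁵ = 0.295 and r̄ is 0.451, so the ratio is √(0.549/0.705) = 0.88 and type I error 8.4%. With same-session 0.7-0.8, adjacent-session 0.5-0.6 and a fall of 10-20% per step, T0-to-T2 type I error was about 7-11% across both reading counts.

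**Check by fitted model.** A REML random-intercept model on simulated data (3 × 36, 5 readings, 0.8 / 0.5, 150 runs) gave a mean model SE of 0.220 for both contrasts. The true values are 0.149 (pre-to-post) and 0.236 (T0 to T1-post).

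**The case against.** **This is analysis-plan detail.** The article condenses, and covariance choices often sit elsewhere. It does not say that the person is the only random effect, nor does it rule out a correction. This has some force. But the article goes beyond naming a method: it states the random effect and the levels of the time term, and that model, run as stated, has the fault.

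**The team's own analysis avoids it.** Results reports multivariate repeated-measures ANOVAs for state anxiety at T1 and T2, and these do not assume equal correlations. True, but that analysis is preliminary, and the analysis section does not commit to it. Leaving both methods open lets the key p-value depend on which is used.

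**The time term may mean two factors.** If phase and before/after are crossed, the arm-by-before/after test has its own error, which under the block correlations above reflects the same-session correlation, and the power loss disappears. This reading is possible. The article does not state it, and T0, with a single reading, does not fit such a crossing.

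**The consequence is limited.** This is a pilot, the sample size rests on the between-groups test, and a too-wide error is conservative. All of that stands, and it limits the priority of the point.

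**A stronger reading.** A reader might infer that the design shows the correlations to be unequal, so that change from T0 will certainly be over-rejected. The documents give timing, not correlations. A relaxation session lies between the two same-session readings, and varied response to it could lower their correlation. Without decay over days the change-from-T0 error is barely affected.

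**Conclusion.** The concern holds in conditional form. As written, the model imposes one correlation on readings whose spacing runs from under an hour to two weeks. If same-session readings correlate more (0.6-0.8 v 0.3-0.5, all assumed), the pre-to-post T1 VR v GI error for STAI-Y1 and the relaxation scale is about 10-80% too wide. The power loss runs from 7-8 points at 0.6 v 0.5 to about 18 points at 0.7 v 0.5 with 13 readings, and more at wider gaps. It does not depend on modelling all 13 readings, since 5 give much the same.

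The change-from-T0 side is minor: 1-7% too narrow and type I error about 5-7%, reaching about 7-11% for T0-to-T2 only if correlation decays over days. In balanced data the arm main effect averaged over occasions is untouched. The sentence covers all outcomes, but the pre-to-post problem arises only for those read before and after sessions. It is worth correcting before the final analysis; it does not invalidate the design or the sample size.

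**What to change.** In Statistical Procedure and Data Analysis, for outcomes read before and after sessions, state one of the following:

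- A mixed model with arm, time and arm-by-time as fixed effects, and either an unstructured covariance (T0, T1 and T2 readings) or a session-within-person random effect added to the person effect (full series).
- The ANOVA, or the multivariate form already used in Results, with Greenhouse-Geisser-corrected omnibus tests where the univariate ANOVA is kept, and each planned contrast (such as T1 post minus pre, VR v GI) tested on that contrast's own variance.

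The choice should be fixed before the final data are analysed. The cost is one sentence, a few more covariance parameters and slightly fewer error degrees of freedom. SPSS and R, both already named, can do either, and no new data are needed.

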## Results

As of July 2022, a total of 45 individuals have been assessed as eligible for study enrollment (Multimedia Appendix 2).

Preliminary data showed adequate Cronbach α for all the T0 self-report questionnaire scores (ranging from .66 to .83). No differences emerged between the GI and VR groups at the baseline (T0) for all the sociodemographics and psychological features investigated (gender, marital status, school attendance, employment, participation in relaxation training in the past, use of VR in the past, anxiety, depressive and stress symptomatology, and the ability to imagine in a vividness way mental images) except for age (*F*_1,39_=12.32; *P*<.001) and years of education (*F*_1,39_=4.81; *P*=.04), factors that have been controlled for in the following group comparisons. To preliminarily investigate the differences between the VR and GI groups in experiencing state anxiety before and after the relaxation session (T1) and at T2, repeated-measures multivariate ANOVAs have been computed. At T1, our preliminary analysis showed a significant difference of the state-anxiety symptoms (*F*_1,39_=22.48*;*
*P*<.001) between groups with lower scores in state anxiety (VR group: mean 30.10, SD 4.35; GI group: mean 39.35, SD 4.71; *t*_1,39_=5.92*;*
*P*<.001) for the VR group after the relaxation session. Moreover, the VR group perceived a higher sense of physical presence (*F*_1,39_=7.38*;*
*P*<.01). The study’s experimental phase is expected to conclude in May 2023, and the results of the research will be presented in June 2023. The results obtained from this work will be published in an open-access scientific paper and in the form of posters and conference papers to be presented at national and international conferences.

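### The arm main effect on which the trial was sized averages over assessments made before any VR exposure; the T0 score would serve better as a covariate on post-session T1 and T2 scores

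*Protocol article*

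**What the plan says.** The Statistical Procedure section of the protocol article plans a mixed-design repeated-measures ANOVA with individuals as the random effect, "while the type of intervention and time (T0/T1/T2/before and after each session) will be the fixed effects". It names no baseline covariate and does not say whether the arm term or the arm-by-time term answers the hypothesis.

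The Power Calculation states that "the repeated-measures ANOVAs between factors have been considered". Its inputs are "The effect size was set as 0.25, the α as .05", a power target of 0.80 and "We have 3 separate groups and 3 measurements", which lead to "at least 36 participants for each of the 3 groups".

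Under Study Design, STAI-Y is given at T0, and STAI-Y1 before and after each of t1-t4, T1 and T2. On the training sessions the article says: "Before and after each relaxation session (t1-t4), in approximately 20 minutes, the personal level of tension is assessed", with STAI-Y1 alongside. The Active Comparator and Intervention A have the same Zoom training at t1-t4, while Intervention B has audio tracks. VR is first used at T1. At T2 all arms do self-guided imagery without the headset.

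The preliminary Results report baseline group differences in age and education, "factors that have been controlled for in the following group comparisons".

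**The concern.** The main hypothesis is that VR lowers state anxiety more than guided imagery. An arm main effect is the arm difference averaged over every time level in the model. At levels before the VR exposure, the Active Comparator and Intervention A can differ only by chance, so each such level pulls the average towards zero and adds noise. The sizing assumes that f = 0.25 holds on that average, T0 included, which randomisation rules out in expectation.

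The arm-by-time term avoids the dilution. If the training sessions are among the levels, though, it also responds to Zoom versus audio, which is a separate aim. A significant result would then not show which aim produced it.

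Meanwhile the T0 STAI-Y1 score, an obvious predictor of later STAI-Y1, is collected in everyone and used only as one more outcome. In the preliminary analysis the covariates were picked because they differed at baseline, not because they were expected to predict the outcome.

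**Working it through.** **Inputs.** From the Power Calculation: f = 0.25, α = 0.05, target power 0.80, 3 groups, 3 measurements, 36 per group (N = 108). The correlation ρ between measurements is not stated. I assume 0.5, show 0.3 to 0.7, and use compound symmetry throughout. Power comes from the noncentral F distribution.

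**The plan's own figure.** Between-factors test: λ = f²·N·m / (1 + (m−1)ρ) = 0.0625 × 108 × 3 / 2 = 10.125, df 2 and 105, power 0.809. The smallest balanced N reaching 0.80 is 108 at ρ = 0.5 (96 at 0.4, 117 at 0.6). The within-between version with the same inputs needs only 36 in total. The trial was therefore sized on the arm main effect, with ρ = 0.5 implied.

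**STAI-Y1 levels.** T0 (1) + t1-t4 before/after (8) + T1 before/after (2) + T2 before/after (2) = 13. Ten precede VR: T0, the eight training scores and T1-before. Three can carry a VR effect.

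**Scenario.** f = 0.25 at the post-exposure levels and zero before.

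- Arm main effect, T0/T1/T2: λ = (0.25 × 2/3)² × 108 × 3 / 2 = 4.5.
- Arm main effect, 13 levels: λ = (0.25 × 3/13)² × 108 × 13 / 7 = 0.67.
- Arm-by-time, 3 levels: λ = 108 × 0.0625 × (2/3) / 0.5 = 9.0, df 4 and 210.
- Arm-by-time, 13 levels: λ = 108 × 0.0625 × (30/13) / 0.5 = 31.15, df 24 and 1260.
- Mean of T1 and T2 adjusted for T0, three-arm test: residual variance (1+ρ)/2 − ρ² = 0.5, λ = 6.75 / 0.5 = 13.5, df 2 and 104.

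| Test | ρ 0.3 | ρ 0.5 | ρ 0.7 |
|---|---|---|---|
| Arm main effect, 3 levels | 0.54 | 0.45 | 0.38 |
| Arm main effect, 13 levels | 0.13 | 0.10 | 0.09 |
| Arm-by-time, 3 levels | 0.49 | 0.65 | 0.88 |
| Arm-by-time, 13 levels | 0.79 | 0.93 | 0.998 |
| T0-adjusted mean of T1 and T2 | 0.88 | 0.91 | 0.98 |

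Simulation of 8,000 trials at ρ = 0.5 gave 0.451, 0.651 and 0.907 for the three-level main effect, the three-level interaction and the adjusted mean.

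**Effect at T1 only.** The adjusted mean carries f = 0.125: λ = 108 × 0.015625 / 0.5 = 3.375, power 0.35 (0.31 to 0.47). The three-level interaction keeps 0.65.

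**Contrast A minus Active Comparator at T1-after.** If A and B share the effect, f = 0.25 means a difference of d = 0.25 × 3/√2 = 0.530 SD. Unadjusted: λ = 18 × 0.530² = 5.06, power 0.61. Adjusted for T0: λ = 5.06 / (1 − 0.25) = 6.75, power 0.73 (0.65 to 0.88).

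**What the 13-level interaction detects.** Suppose VR has no effect and audio differs from Zoom with f = 0.25 at the eight t1-t4 scores only. Then λ = 6.75 × (40/13) / 0.5 = 41.5, and the interaction rejects with probability 0.99. The arm main effect, with λ = (0.25 × 8/13)² × 108 × 13 / 7 = 4.75, rejects with probability 0.47. A T0-adjusted test of post-session T1 and T2 scores stays at 0.05 if the audio difference does not carry over.

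**The case against.** The strongest defence is that a mixed ANOVA is normally read through its arm-by-time term, which is valid and is not diluted. Under the same assumptions it has 0.93 power with 13 levels, slightly above the 0.91 of the adjusted mean. This stands as a statement about power. It does not settle which hypothesis the test addresses, because audio training alone can make that term significant.

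Modelling t1-t4 is also not an error in itself. Zoom versus audio is an aim, and Table 1 asks for scores before and after each session. The article never declares the arm main effect to be the VR test, and the preliminary analysis compared groups after the T1 session. That the arm effect matters is inferred from the sizing, so the defect is a mismatch between sizing, model and hypothesis.

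A reader might infer that the planned analysis has 45 to 65% power on mostly VR-free assessments, and that adjustment lifts this to 91%. The documents do not support that. VR-free levels are the majority only in the 13-level model (10 of 13), whereas 0.45 and 0.65 belong to the three-level model, and 0.65 is its interaction test. The 0.91 belongs to a three-arm test on the mean of T1 and T2, needs an equal effect at both visits, and is not the power of the A-versus-comparator contrast. The covariate supplies only part of it: at ρ = 0.5, the mean of T1 and T2 without a covariate already has 0.76.

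The age and education adjustment is reported only for the preliminary analysis. The article states no missing-data rate or complete-case rule, so no loss from missing data is claimed here.

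**Conclusion.** The point holds in limited form. The effect used for sizing does not match the hypothesis: for VR versus guided imagery its power is 0.45 (0.54 to 0.38 as ρ rises from 0.3 to 0.7) with T0/T1/T2, and 0.10 (0.13 to 0.09) with all 13 levels. The interaction has adequate power with 13 levels but does not isolate VR. With three levels it has 0.65 (0.49 to 0.88).

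Adjusting post-session scores for T0 gives a test aimed at the hypothesis and lifts the A-versus-comparator contrast at T1-after from 0.61 to about 0.73. That is still below 0.80 at ρ = 0.5. The figures rest on f = 0.25 in single-assessment SD units, compound symmetry, an unstated ρ, complete data and, for the contrast, the same effect in A and B. In a self-described pilot this is recommended rather than essential.

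**What to change.** - Replace the ANOVA sentence for STAI-Y1 with a linear mixed model on the scores after the T1 and T2 sessions, with arm, visit, arm-by-visit and the T0 STAI-Y1 score as fixed effects.
- Name Intervention A minus Active Comparator after the T1 session as the primary contrast, with its 95% CI.
- Analyse t1-t4 separately for Zoom versus audio.
- Use each scale's own T0 score as covariate wherever one exists. This excludes sense of presence, which is measured only at T1 and T2.
- Fix any further covariates in advance for their expected relation to the outcome, not by baseline significance.
- Restate power as a range over ρ, for the contrast actually named and with the assumption about T2 spelled out.

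The cost is a rewritten paragraph and a few lines of code. The T0 scores are already collected, and the covariate uses one degree of freedom.
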